### Study design and intervention

The diagram for Standard Protocol Items: Recommendations for Interventional Trials (SPIRIT) is shown in Fig. 2. After recruiting participants, participants will be stratified based on age (20 to 40 and 40 to 60 years), gender (male/female), BMI (18.5 to 24.9 and 25 to 30), and type of medicines (anti-inflammatory and immunosuppressant) into different blocks and will be randomly allocated to the intervention or control groups. For each patient in a certain block, a matched person in terms of abovementioned variables would be placed in that block. Then, these two patients in a given block would be randomly assigned to the intervention and control groups. To do randomization, an identification code will be given to each eligible patient, and then, code of patients with the same age, gender, BMI, and medication will be stated in the lottery container, and finally, patients with the same conditions will be randomly assigned to the intervention or control groups. Random allocation will be done by a person who is unaware about the aim of our study. Patients in the intervention group (*n* = 15) will receive 250 mL/day preservative-free soy milk along with routine treatments that they were taking for their condition. Participants in the control group (*n* = 15) will receive only routine treatments. The intervention will last for 4 weeks. The assessment of primary and secondary outcome variables will be done at the study baseline and end of trial. Participants in both groups will also receive usual dietary recommendations for IBD patients based on European Society for Parenteral and Enteral Nutrition (ESPEN) guideline [32]. This guideline will be explained to patients by an experienced nutritionist. Given that preservative-free soy milk will be expired within 12 days after production, three 1-L bottles of soy milk will be delivered to patients in intervention group every 12 days (at the study baseline, day 12, and day 24). At the study baseline and day 12, patients in the intervention group will received 3 1-L bottles of soy milk (used during 12 days), and at day 24, they will received 2 1-L bottles of soy milk (used during 8 days). Due to the unfavorable taste of soy milk, patients in intervention group will be asked to consume it at night before sleep. They should consume a 250-mL glass of soy milk every night. Participants will be instructed in a class, prior to the start of trial, about the quantity of soy milk they have to consume in a day. A standard glass (which contained 250 mL soy milk) will be shown to participants, and all will be asked to use the same glass to make sure that the daily portion they are consuming is the one the investigators requested. To control this, participants will be contacted every day and they will be asked to send us the photo of the glass they are using for soy milk drinking. At each delivery of soy milk bottles, patients will be monitored for soy milk consumption and will be asked to give back the empty bottles. Participants’ compliance will be assessed using the following formula: (number of used packages/all given packages) × 100. In addition to assessment of compliance, consumption of soy milk will be monitored by phone call every week. In addition, collecting three 1-day dietary recalls from participants throughout the study can further help computing the compliance to soy milk intake. Participants will be asked not to change their lifestyle, dietary habits, and medicines during the study.

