**Methods:**

This study is a randomized clinical trial, in which thirty patients with mild to moderate severity of UC will be randomly allocated to receive either 250 mL/day soy milk plus routine treatments (*n* = 15) or only routine treatments (*n* = 15) for 4 weeks. Assessment of anthropometric measures and biochemical indicators including serum concentrations of high-sensitivity C-reactive protein (hs-CRP), tumor necrosis factor-α (TNF-α), interleukin-1β (IL-1β), and interferon gamma (IFN-γ) will be done at the study baseline and end of trial. In addition, the quantity of butyrate-producing bacteria including *Clostridium* cluster IV, *Faecalibacterium prausnitzii*, and *Roseburia* spp.; prebiotic bacteria including *Lactobacillus* spp. and *Bifidobacteria* spp.; and mucus-degrading bacteria including *Akkermansia muciniphila*, *Bacteroides fragilis*, and *Ruminococcus* spp., as well as calprotectin and lactoferrin levels, will be explored in fecal samples. Also, the *Firmicutes* to *Bacteroidetes* ratio which is of significant relevance in human gut microbiota composition will be assessed.

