
**Fig. 2 Fig2:**
[figure not shown]
Standard Protocol Items: Recommendations for Interventional Trials (SPIRIT) chart of the enrolments and assessments during randomized controlled trials. The “X” refers to what is done in the given period. Abbreviations: IBD, inflammatory bowel disease; WK, week

To assess dietary intakes throughout the study, we will fill 3 1-day dietary recalls (including two working days and a non-working day) at weeks 2, 3, and 4 of intervention by telephone interview. Dietary recall format is presented in Supplementary file, section B. To complete the dietary recalls, participants will be asked to report dietary intakes based on household measures. Then, we will convert household measures to grams using available booklets. The average of dietary intakes in these 3 days will be considered as participants’ dietary intakes throughout the intervention. To obtain nutrient intakes on the basis of these food recalls, we will use Nutritionist IV software (based on US National Nutrient Databank) modified for Iranian foods.

In addition, 2 1-day physical activity records (including a working day and a non-working day) will be gathered from all patients at weeks 2 and 4 of intervention to assess physical activity during the study. The format of physical activity record is shown in Supplementary file, section C. All participants will be educated how to record their activities throughout the study before the start of the trial. Furthermore, patients in both groups will be asked not to change their physical activity throughout the trial.

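### The itemised soy milk deliveries cover 32 days, but the 4-week intervention needs 28 days' supply, so exposure or the bottle-count compliance score may be off

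*Protocol article*

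**What the plan says.** All of this is in the protocol article, mainly under Study design and intervention.

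- **Dose.** Patients in the soy milk arm "will receive 250 mL/day preservative-free soy milk along with routine treatments", and the instruction is explicit: "They should consume a 250-mL glass of soy milk every night".
- **Duration.** "The intervention will last for 4 weeks". The abstract's Methods paragraph gives the same length.
- **Deliveries, general sentence.** Because the product expires after 12 days, "three 1-L bottles of soy milk will be delivered to patients in intervention group every 12 days", with baseline, day 12 and day 24 named as the delivery days.
- **Deliveries, itemised sentence.** Three bottles at baseline and three at day 12, each set lasting 12 days; then "at day 24, they will received 2 1-L bottles of soy milk (used during 8 days").
- **Compliance.** A percentage: "number of used packages/all given packages) × 100". Empty bottles are handed back at each delivery.
- **Other checks on intake.** Daily contact with a photo of the glass, a weekly phone call, and dietary recalls "at weeks 2, 3, and 4 of intervention by telephone interview".

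**The concern.** Dose, duration and supply should agree, and they do not. The last delivery comes at day 24, when 4 days of a 28-day intervention remain, yet the article sends enough for 8 days and says the bottles are used over 8 days.

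Two quantities depend on this. One is how long patients are exposed: a patient who uses the last delivery as described drinks past the stated end of the intervention. The other is the compliance percentage. Its denominator is everything given, so a bottle that is not needed lowers the score of a patient who did exactly what the 4-week prescription asks. The Strengths section lists compliance assessment among the trial's merits, so the score ought to return 100% for full adherence.

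**Working it through.** **Inputs** (Study design and intervention): 0.25 L per day; 4 weeks = 28 days; 1 L bottles; itemised deliveries of 3, 3 and 2 bottles at baseline, day 12 and day 24; compliance = used ÷ given × 100.

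**Step 1. Reproduce the article's own bottle-to-day figures.** Days = litres ÷ 0.25.

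- 3 ÷ 0.25 = 12 days, as stated for baseline and day 12.
- 2 ÷ 0.25 = 8 days, as stated for day 24.

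Each single delivery is therefore computed correctly. The problem lies in the total.

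**Step 2. Total supply.** 3 + 3 + 2 = 8 bottles; 8 ÷ 0.25 = 32 days. Equivalently, 12 + 12 + 8 = 32, and day 24 plus 8 days runs to day 32.

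**Step 3. Need.** 28 × 0.25 = 7 L = 7 bottles. After day 24 the need is (28 − 24) × 0.25 = 1 L = 1 bottle.

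**Step 4. Excess.** 8 − 7 = 1 bottle; 32 − 28 = 4 days; 4 ÷ 28 = 14.3%.

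**Step 5. What this does to exposure and to the score of a patient who never misses a glass.**

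| How the day-24 delivery is handled | Exposure | Compliance |
|---|---|---|
| Both bottles used over 8 days | 32 days | 8/8 = 100% |
| Patient stops at day 28, surplus counted as given | 28 days | 7/8 = 87.5% |
| Patient stops at day 28, surplus not counted as given | 28 days | 7/7 = 100% |

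Only the third row gives both the planned exposure and a full score, and it needs a counting rule that the article does not state. The second row follows the literal wording of the formula.

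**Step 6. Check of the fix.** 3 + 3 + 1 = 7 bottles; 7 ÷ 0.25 = 28 days.

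**The case against.** The best reply is that the extra bottle is a harmless spare. The parenthesis about 8 days has the same form as the one about 12 days, and may say only how long 2 L lasts at the prescribed dose. The explicit statement of length is 4 weeks, the last dietary recall falls in week 4, and nothing is scheduled later. Patients are contacted daily, so an unnoticed overrun is unlikely. The article describes empties being returned at deliveries, and the last delivery is at day 24, so it does not say how the day-24 bottles are counted. That detail may be in the full protocol.

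Much of this stands. Drinking to day 32 is possible but not clearly intended, and 87.5% depends on the surplus staying in the denominator. It would therefore be too strong to infer that exposure or compliance must be wrong: the 7/7 case leaves both correct. What does not stand is the idea that the text itself resolves the matter. It calls no bottle a reserve, and it gives the second day-24 bottle a period of use. The 12-day shelf life explains the delivery interval but not two bottles for 4 remaining days. This is also not a detail left out of a condensed article, because the figures printed conflict with one another.

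A reader might also take the general sentence at face value: three deliveries of three bottles, so 9 bottles, 9 ÷ 0.25 = 36 days, and 7/9 = 77.8% for full adherence. The text does not support treating that as the plan. The next sentence itemises each delivery and governs; the general one mainly conveys the 12-day rhythm. Its count for day 24 is loose wording to be tidied, not a second supply error.

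**Conclusion.** The point holds as a minor inconsistency, wrong as written. The itemised schedule supplies 8 bottles where 7 are needed. Read literally, that means either 4 extra days of soy milk (14%) or a score of 87.5% for a fully adherent patient who stops at day 28. The 87.5% assumes that the surplus bottle counts as given; without that assumption the score is 100%.

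A reader might go further and infer that the treatment comparison is compromised, or that the end-of-trial measurements slip to day 32. The article supports neither. It sets no adherence threshold, the exclusion criteria do not remove patients for low compliance, and neither the sample size calculation nor the planned tests use the score. End of trial is given no day number, but it belongs to an intervention stated to last 4 weeks. If all soy milk patients are handled alike, the shift in the score is the same for each of them and can be undone afterwards by changing the denominator. The photos, calls and recalls check intake separately; they limit the harm but do not correct the schedule or the formula.

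**What to change.** Choose one of two remedies:

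1. Deliver one bottle at day 24 and change its stated period of use to 4 days.
2. Keep two bottles, label the second as a reserve, and compute compliance against the 7 bottles that 28 days require.

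In either case, reword the general delivery sentence so that it gives the 12-day interval without implying three bottles at day 24.

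The cost is a change of wording. The first remedy also saves one bottle per soy milk patient. Neither adds a visit or a measurement.

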
**Fig. 2 Fig2:**
[figure not shown]
Standard Protocol Items: Recommendations for Interventional Trials (SPIRIT) chart of the enrolments and assessments during randomized controlled trials. The “X” refers to what is done in the given period. Abbreviations: IBD, inflammatory bowel disease; WK, week

To assess dietary intakes throughout the study, we will fill 3 1-day dietary recalls (including two working days and a non-working day) at weeks 2, 3, and 4 of intervention by telephone interview. Dietary recall format is presented in Supplementary file, section B. To complete the dietary recalls, participants will be asked to report dietary intakes based on household measures. Then, we will convert household measures to grams using available booklets. The average of dietary intakes in these 3 days will be considered as participants’ dietary intakes throughout the intervention. To obtain nutrient intakes on the basis of these food recalls, we will use Nutritionist IV software (based on US National Nutrient Databank) modified for Iranian foods.

In addition, 2 1-day physical activity records (including a working day and a non-working day) will be gathered from all patients at weeks 2 and 4 of intervention to assess physical activity during the study. The format of physical activity record is shown in Supplementary file, section C. All participants will be educated how to record their activities throughout the study before the start of the trial. Furthermore, patients in both groups will be asked not to change their physical activity throughout the trial.

### Assessment of variables

A standard questionnaire will be used to obtain information on age, gender, education, economic status, medical history, medication use, smoking, and duration of UC. In addition, primary outcomes including serum concentrations of inflammatory biomarkers, fecal concentrations of calprotectin and lactoferrin, quantity of selected bacteria, IBD severity, and disability as well as secondary outcomes including complete blood counts (CBC), erythrocyte sedimentation rate (ESR), quality of life, mental health, anthropometric measures, and blood pressure will be measured at the beginning and end of study.

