### Sample size calculation

Considering the type I error of 5% (*α* = 0.05) and type II error of 20% (*β* = 0.20, power = 80%) and fecal concentrations of calprotectin as the key variable, we manually, without the use of any software, calculated required sample size using the following formula [30]:
$$ n=\frac{2\left[{\left(a+b\right)}^2\times {\upsigma}^2\right]}{{\left({\mu}_1-{\mu}_2\right)}^2} $$

*n* = sample size in each group.

*μ*_1_ = mean for fecal calprotectin in the intervention group (we considered it as 424 μg/g based on the study of Morshedzadeh et al. [31]).

*μ*_2_ = mean for fecal calprotectin in the control group (which was considered as 602 μg/g based on the study of Morshedzadeh et al. [31]).

σ = variance (SD) for mean concentrations of calprotectin, which was considered as 141 (the average SDs reported for fecal calprotectin in the control and intervention groups of Morshedzadeh et al.’s study [31]).

*a* = conventional multiplier for alpha = 0.05 that was 1.96.

*b* = conventional multiplier for power = 0.80 that was 0.842.

Overall, based on the formula and given a 50% drop-out in each group, we will need a sample size of 15 persons for each group. Due to frequent visits (about 6 visits) that each participant would have throughout the study, we considered the drop-out rate as much as 50%. However, we would try our best to keep the drop-outs as low as possible.

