### Biochemical assessments

After 12 h of fasting, a 10-mL venous blood sample will be taken from each patient at the study baseline and end of trial. Total CBC, hemoglobin concentrations, and hematocrit will be measured by a cell counter. Erythrocyte sedimentation rate will be measured using the Wintergreen method. Then, serum will be isolated from the whole blood and will be stored at − 70 °C until further analysis. Serum concentrations of inflammatory cytokines, including high-sensitivity C-reactive protein (hs-CRP), Tumor necrosis factor-α (TNF-α), interleukin-1β (IL-1β), and interferon gamma (IFN-γ) will be measured by the enzyme-linked immunosorbent assay (ELISA) commercial kits. Earlier studies have shown that hs-CRP, TNF-α, IL-1β, and IFN-γ concentrations are positively associated with severity of IBD, particularly UC [33].

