### Gut microbiota and fecal calprotectin

From each individual, 10-g stool sample will be taken to examine gut microbiota and fecal levels of calprotectin and lactoferrin at the study baseline and end of trail. A clean and screw-top container labeled with patient’s code and the date will be given to each patient for fecal sample collection. Participants will be asked to do fecal sampling in the morning. To decrease the changes in the quantity of bacteria in fecal samples after sampling, samples will be frozen at − 70 °C within 2 h after sampling. To take care of this, we will use three approaches: First, we will ask patients to come to the study lab at the day of stool sampling. All the necessary facilities will be available to do fecal sampling in the lab. Second, if the first approach did not work for a patient, we will ask him/her to bring the sample within2 h to the lab. Third, if he/she was not able to do the second approach, we will ask patients to call the study investigators and then somebody from the team would go the patients’ home and take the sample to the lab. The samples will be kept at − 70 °C until further analysis. Total DNA from stool samples will be extracted using the QIAamp (QIAGEN) commercial fecal DNA kits. In addition, the quantity of butyrate-producing bacteria including *Clostridium* cluster IV, *Faecalibacterium prausnitzii*, and *Roseburia* spp.; prebiotic bacteria including *Lactobacillus* spp. and *Bifidobacteria* spp.; and mucus-degrading bacteria including *Akkermansia muciniphila*, *Bacteroides fragilis, Ruminococcus* spp., as well as *Firmicutes* and *Bacteroidetes*, will be determined using the quantitative real-time polymerase chain reaction (qRT-PCR) which will be done by the LightCycler® 96 SW 1.1 instrument (Roche, Germany). Each reaction mixture contains SYBR Premix Ex Taq II (Takara, China), specific primers, and DNA template. In order to design primers, we will use sequence of primers used in the earlier studies [34, 35]. Selection of taxa was based on their correlation with UC and their effectiveness on gut microbiota balance [36]. It has been proposed that mucus-degrading bacteria have an important role in the etiology of UC which is defined as an intestinal mucosal disorder [36]. Also, most selected bacteria are involved in production of short-chain fatty acids (SCFAs), particularly butyrate, which are important metabolites in maintaining intestinal homeostasis [37, 38]. SCFAs are the important fuel for intestinal epithelial cells, are known to strengthen the gut barrier function, and activate signaling cascades that control immune functions and consequently intestinal inflammation [38]. Based on the previous studies, UC patients not only show reduced levels of SCFAs-producing bacteria in intestinal mucosa and feces, but the actual steady-state levels of SCFAs herein also appear to be less than healthy controls [39, 40]. Furthermore, in most clinical trials on patients with intestinal disorders such as UC or irritable bowel syndrome, these taxa were evaluated [34, 41].

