
In addition to fecal microbiota, fecal concentrations of calprotectin and lactoferrin will be measured using the ELISA commercial kits. Calprotectin is a calcium binding protein commonly derived from neutrophils and monocytes and in a less extent from macrophages [42]. Calprotectin is found in stool and plasma, and its concentration increases throughout inflammatory conditions, including IBD and infection [43]. Lactoferrin is a glycoprotein expressed by activated neutrophils [44]. This factor is sensitive and specific for detecting inflammation in chronic IBD [44].

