### Statistical analysis

The Kolmogorov-Smirnov test will be used to examine normal distribution of variables. Log transformation will be conducted for the non-normally distributed data. To examine differences in qualitative variables between soy milk and control groups, we will use the chi-square test. We will apply the independent sample *t* test to detect differences in quantitative variables between the soy milk and control groups. In addition, mentioned test will be used to compare between-group changes in outcome variables. To do within-group comparison, we will use the paired-sample *t* test. Multivariate analysis of covariance (ANCOVA), as a general linear model, will be used to examine the effects of soy milk consumption on outcome variables. In this analysis, baseline value of outcome variables and potential confounding variables which are different between the intervention and control groups will be adjusted to avoid potential risk of bias and detect independent results. All statistical analyses will be done using the SPSS software version 18 (SPSS, Inc. Chicago, IL, USA). *P* < 0.05 will be considered significant.

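### Between 16 and 19 outcomes are co-equal primaries tested at an unadjusted P < 0.05, while the trial is sized on fecal calprotectin alone

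*Protocol article*

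**What the plan says.** Assessment of variables names "primary outcomes including serum concentrations of inflammatory biomarkers, fecal concentrations of calprotectin and lactoferrin, quantity of selected bacteria, IBD severity, and disability". The same sentence goes on to a separate secondary list, so the primary label is deliberate. No member of the primary list is placed above another.

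The Sample size calculation takes a different view of what the trial tests. It uses "fecal concentrations of calprotectin as the key variable", with a type I error of 5% and 80% power, and arrives at 15 patients per group.

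Statistical analysis gives four procedures for quantitative data: an independent t test between groups, the same test on changes in outcomes, a paired test ("To do within-group comparison, we will use the paired-sample" t test), and an ANCOVA adjusted for the baseline value and for confounders that differ between groups. A single threshold covers all of them: P below "0.05 will be considered significant". The section does not say which outcome or which analysis decides the trial.

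**The concern.** The two sections disagree on what the trial is designed to show. One commits the whole 5% to calprotectin. The other gives calprotectin the same standing as 15 or more other outcomes, each judged at 5%. A reader of the final report could not tell whether a positive result on, say, one bacterial group and a null result on calprotectin means that the trial succeeded or failed.

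Two consequences follow. The chance of at least one false-positive primary is well above the 5% used for sizing. In addition, within-arm paired tests invite the statement that soy milk patients improved significantly and controls did not, which is not a comparison of the arms.

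**Working it through.** **Step 1: the plan's own sample size.** Inputs from Sample size calculation: means 424 and 602 μg/g, SD 141, multipliers 1.96 and 0.842.

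n = 2 × (1.96 + 0.842)² × 141² / 178² = 9.85, so 10 per arm. The stated 15 is 10 × 1.5. (Allowing for 50% drop-out by division gives 10 / 0.5 = 20; that is a separate matter.) The multiplier 1.96 shows that the full two-sided 5% is spent on this one outcome.

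**Step 2: counting the primaries.**
- Serum markers (Biochemical assessments): hs-CRP, TNF-α, IL-1β, IFN-γ = 4
- Fecal markers ("fecal concentrations of calprotectin and lactoferrin will be measured using the ELISA commercial kits") = 2
- qPCR targets (Gut microbiota and fecal calprotectin): 3 butyrate producers, 2 in the prebiotic group, 3 mucus degraders, 2 phyla = 10
- Partial Mayo score = 1; IBD-DI composite = 1

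Total: 4 + 2 + 10 + 1 + 1 = 18. Adding the Firmicutes/Bacteroidetes ratio, which the Abstract says will be assessed, gives 19. Leaving out the phyla and the ratio gives 4 + 2 + 8 + 2 = 16. Limitations counts six biomarkers and 9 genes, which gives 6 + 9 + 2 = 17.

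**Step 3: family-wise error, independent outcomes, one test each.** Formula: 1 − 0.95^m.

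| m | Chance of at least one false positive |
|---|---|
| 16 | 56.0% |
| 17 | 58.2% |
| 18 | 60.3% |
| 19 | 62.3% |

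**Step 4: correlated outcomes.** The documents give no correlations, so this is a simulation under assumed values: no effect on any outcome, 18 outcomes, 15 per arm, baseline-to-end correlation 0.5, and equal correlation between all outcomes. The three between-group analyses are the t test on end values, the t test on change, and the baseline-adjusted ANCOVA. Repeated runs gave the spreads shown.

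| Correlation between outcomes | One ANCOVA per outcome | Positive on any of the three |
|---|---|---|
| 0 | 59–60% | 83–84% |
| 0.3 | 51–54% | 75–77% |
| 0.5 | 42–44% | 64–65% |
| 0.7 | 29–30% | 48% |

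The first row agrees with the exact 60.3% of Step 3. For a single outcome, counting any of the three analyses raises the error from 5% to about 10%.

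**Step 5: paired tests.** Assume that both arms improve by the same amount d, in SD units of the change, with 15 per arm. If each arm's paired t test has power p, exactly one arm is significant with probability 2p(1 − p). At d = 0.5, p = 0.438, which gives 2 × 0.438 × 0.562 = 49%.

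| d | Exactly one arm significant |
|---|---|
| 0.2 | 20% |
| 0.3 | 31% |
| 0.5 | 49% |
| 0.8 | 29% |
| 1.0 | 10% |

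The true difference between arms is zero in every row.

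**The case against.** **The outcomes are unlikely to be independent.** This stands. Biochemical assessments says that the four serum markers rise with disease severity, which is itself on the list. Calprotectin and lactoferrin both come from neutrophils, and the ratio is computed from two other listed items. For one test per outcome, 56–62% is therefore best read as an upper figure.

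**A reader might infer that a chance positive primary is more likely than not.** The documents do not support that as a flat statement. With one test per outcome, it fails once the average correlation goes somewhat above 0.3. It holds up to about 0.7 only if a positive on any of three analyses counts as success, and the protocol states no such rule. It states no success criterion at all.

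**The methods have distinct roles.** This stands in part. ANCOVA is the analysis tied to the effect of soy milk, and the plain t test may be meant partly for baseline comparison. The change-score t test, however, is explicitly assigned to outcomes, and neither it nor ANCOVA is made decisive. Calling the ANCOVA multivariate does not make it one joint test, because it adjusts for outcome baselines and the separate t tests remain.

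**Paired tests are not declared to be evidence of efficacy.** True. The risk lies in how they are read, and 49% is near the top of the 10–49% range.

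**A statistical analysis plan may hold a multiplicity rule.** It may, and the absence of one here is not the point. The co-equal primary list, the blanket threshold and the single-outcome sizing are all written in this document. A later rule would have to change one of them.

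**Conclusion.** The point holds as a conflict within the protocol. The 5% used for sizing applies to calprotectin, and it does not hold for a primary set of 16 to 19 unranked outcomes each tested at 5%. Under no effect on any outcome, the chance of at least one false-positive primary ranges from about 29% (one test each, correlation 0.7) to 62% (one test each, 19 independent outcomes). It is about 48–84% for 18 outcomes if any of the three between-group analyses may count. The correlated figures rest on assumed equal correlations between outcomes, a baseline-to-end correlation of 0.5 and 15 completers per arm. The lowest is still almost six times the nominal level. The paired-test figure of 10–49% rests on an assumed equal improvement of 0.2 to 1.0 SD in both arms. The conflict should be settled before analysis, because it governs what the trial may conclude.

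**What to change.** In Assessment of variables, name end-of-trial (week-4) fecal calprotectin as the sole primary outcome, in line with the sample size section. List the other outcomes as secondary or exploratory, reported with 95% confidence intervals.

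In Statistical analysis, name the baseline-adjusted ANCOVA of calprotectin as the single confirmatory test at two-sided 5%. Describe the change-score t test as supportive, and the paired t tests as descriptive only, not as evidence of effect.

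Record the change as a protocol and registry amendment. It is therefore more than a wording edit, but this point adds no patients. What is lost is any confirmatory claim on bacteria, cytokines, lactoferrin, severity or disability, for which the trial was not sized. This narrows the formal question compared with the stated aims.

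The alternative is to keep all primaries, split alpha and re-size. Bonferroni over 18 outcomes gives 0.05 / 18 = 0.0028 per test (multiplier 2.991), so n = 2 × (2.991 + 0.842)² × 141² / 178² = 18.4. That is 19 evaluable patients per arm instead of 10, for the calprotectin effect alone. Limitations says that a larger sample is not affordable, which favours the single primary outcome.
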